### Study population

Three hundred participants provided consent and were recruited to CROSSFIRE from 19 participating hospital sites: 164 participants in the randomised trial and 136 in the observational study. No patients declined participation in the observational study.

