Significantly lower rates of major complications (including deep infection, reoperation, neuropathy, tendon irritation requiring treatment, tendon rupture, fracture non-union, and implant failure, complex regional pain syndrome, death) at 3 and 12 months post treatmentSuperior (closer to normal) radiographic outcomes (ulnar variance and articular step (millimetres), dorsal angulation and radial tilt (degrees)) at post reduction and 6 weeks or moreSuperior PRWE scores at 3 months, 2, 5 and 10 years to a level of clinical importanceSuperior DASH scores at 12 months, to a level of clinical importance. A difference of greater than 11 points will be considered to be clinically important [33]Superior health-related quality of life (EQ-UI and EQ-VAS scores at 3 months and 12 months, 2, 5 and 10 years to a level of clinical importance. A difference of greater than 0.1 points in the EQ-UI score has previously been used as the minimal clinically important difference (MCID) in orthopaedic surgery [34] and musculoskeletal [35] contexts and will be considered to be clinically important. A difference of 10 on the EQ-VAS has been reported as the MCID and will be considered to be clinically important [36]Lower patient-reported pain (numerical rating scale NRS) at 3 months and 12 months, 2, 5 and 10 years to a level of clinical importance. A systematic review on the MCIDs of Visual Analogue Scales (VAS) used for assessment of acute pain reported that the median MCID was 17 mm on a 100-mm scale [37]. Given that the NRS uses whole integers between 0 and 10, a value of 2 points or greater will be considered to be clinically importantSuperior patient-reported treatment success at 12 months, 2, 5 and 10 years (measured on a 5-point Likert scale)Less patient-rated bother with appearance at 12 months, 2, 5 and 10 years (measured on a 5-point Likert scale)Lower therapy utilisation up to and at 3 months as measured by the prevalence of therapy utilisation at 3 months

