### Power and sample size

We consider 14 points on PRWE to be the minimum clinical difference necessary to justify the additional costs of surgery compared to non-surgical treatment. This is the MCID determined by Sorensen [32] and larger than the 11.5-point estimate determined by Walenkamp [38].

A total of 128 patients (64 in each group) will provide 90% power to detect a difference of 14 points on the PRWE scale at a significance level of 0.05. We aim to recruit 160 patients to allow for 20% loss to follow-up. Two previous RCTs that had each published results at the time of our sample size calculation reported loss-to-follow-up rates of 19% [5, 39]. Given that this is a multi-centre trial, the closing date for recruitment (31 December 2018) was set based on expected recruitment of 160 randomised participants. However, by the time recruitment closed, 164 participants had been recruited.

The observational arm includes all eligible patients not consenting to randomisation. We recruited 136 participants to the observational arm to the trial.

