### Statistical analysis

#### Analysis principles

Data will be analysed using statistical analysis package SAS (SAS Institute Inc., Cary, NC, USA) and R statistical computing software [40].

Recruitment for CROSSFIRE concluded in January 2019. The final analysis will commence after the 12-month data collection is complete. The de-identified data-set will be inspected for missing data and data quality.

Study outcomes produce both continuous and categorical data. Continuous data will be inspected for normality. Continuous data will be presented by mean values and standard deviations (SDs) as well as mean difference (MD) and 95% confidence interval (CIs) (see Tables 4 and 5 as examples) if normally distributed, otherwise by median and interquartile range.

**Table 4 Tab4:** Secondary outcomes at 3 months for the randomised group

Outcome		Randomised		
		Surgical (*n*=__)	Non-surgical (*n*=__)	MD (95%CI) or odds ratio (95%CI)
PRWE, mean (SD)				
ED-5D-5L, mean (SD)	EQ-UI			
	EQ-VAS			
Pain on NRS (0-10)				
Patient-reported treatment success n(%)	Very successful			
	Successful			
	Neutral			
	Unsuccessful			
	Very unsuccessful			
Therapy utilisation up to 3 months (Yes/No) n(%)				
Therapy utilisation at 3 months (Yes/No) n(%)				
Radiographic measures, mean (SD)	Dorsal angulation (degrees)			
	Radial tilt (degrees)			
	Ulnar variance (mms)			
	Articular step (mms)

**Table 5 Tab5:** Secondary outcomes at 3 months for the observational group

Outcome		Observational		
		Surgical (*n*=__)	Non-surgical (*n*=__)	MD (95%CI) or odds ratio (95%CI)
PRWE, mean (SD)				
ED-5D-5L, mean (SD)	EQ-UI			
	EQ-VAS			
Pain on NRS (0-10)				
Patient-reported treatment success n(%)	Very successful			
	Successful			
	Neutral			
	Unsuccessful			
	Very unsuccessful			
Therapy utilisation up to 3 months (Yes/No) n(%)				
Therapy utilisation at 3 months (Yes/No) n(%)				
Radiographic measures, mean (SD)	Dorsal angulation (degrees)			
	Radial tilt (degrees)			
	Ulnar variance (mms)			
	Articular step (mms)			

Categorical data will be summarised according to frequency (*n*) and incidence (%) (see Table 5). Comparison between treatment groups will be tested using chi-squared and odds ratio with 95% CI.

Comparisons between treatment groups will be tested at the two-sided, 5% significance level. *P* values will be reported to three decimal places if *P* > 0.001. *P* values < 0.001 will be reported as < 0.001. Means and SDs will be reported to one decimal place.

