Tendon irritation requiring treatment	*n* (%)	*n* (%)	
Tendon rupture	*n* (%)	*n* (%)	
Fracture non-union at 6 months	*n* (%)	*n* (%)	
Implant failure	*n* (%)	*n* (%)	
CRPS	*n* (%)	*n* (%)	
Death	*n* (%)	*n* (%)	
Any complications	*n* (%)	*n* (%)	

*CI* confidence interval, *CRPS* chronic regional pain syndrome

**Table 9 Tab9:** Complications for observational group

Complication; frequency (incidence)	Randomised group		
	Surgical (*n* = _)	Non-surgical (*n* = _)	Odds ratio (95% CI)
Deep infection	*n* (%)	*n* (%)	
Reoperation	*n* (%)	*n* (%)	
Neuropathy	*n* (%)	*n* (%)	
Tendon irritation requiring treatment	*n* (%)	*n* (%)	
Tendon rupture	*n* (%)	*n* (%)	
Fracture non-union at 6 months	*n* (%)	*n* (%)	
Implant failure	*n* (%)	*n* (%)	
CRPS	*n* (%)	*n* (%)	
Death	*n* (%)	*n* (%)	
Any complications	*n* (%)	*n* (%)	

*CI* confidence interval, *CRPS* chronic regional pain syndrome

Repeated measures analysis will be used for the following:
Continuous variables measured at 3 months and 12 months include EQ-5D-5L (UI and VAS scores), pain on NRS (0–10) and radiographic measures (dorsal angulation, radial tilt, ulnar variance and articular step). These measurements will be analysed using analysis of variance (ANOVA) with repeated measuresCategorical variables measured at 3 months and 12 months include patient-reported treatment success (Likert) and patient-reported bother with appearance (Likert). See Additional file 1 for question format. These variables will be analysed by contingency table to compare the frequency of treatment success categories between the two randomised groups. Results will be displayed as odds ratio with 95% CIs (see Table 4 for example)

The observational group will be used to investigate potential selection bias. Baseline characteristics will be compared between the observational group and the randomised group (see Table 10 for example).

**Table 10 Tab10:** baseline characteristics for the randomised and observational arms of trial

Baseline measure		Randomised arm (*n*=__)	Observational arm (*n*=__)
Age (years), mean (range)			
Gender n (%)	Female		
	Male		
Fracture type n (%)	23A		
	23C		
Radiographic features, mean (SD)	Dorsal angulation (degrees)		
	Radial tilt (degrees)		
	Ulnar variance (mms)		
	Articular step (mms)		
Co-morbidities, n (%)	Diabetes? (Y/N)		
	Smoker? (Y/N)		
	Glucocorticoid treatment? (Y/N)		
	Osteoporosis treatment? (Y/N)		

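### The two five-level ordered outcomes get a comparison that ignores their order and an odds ratio that is not defined, and the plan contradicts itself on whether they are measured at 3 months

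*SAP article*

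**What the plan says.** Under Analysis principles the SAP article sets the rule for all categorical data: "Comparison between treatment groups will be tested using chi-squared and odds ratio with 95% CI". Testing is two-sided at 5%: "Comparisons between treatment groups will be tested at the two-sided, 5% significance level".

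Under Secondary analysis, in the list introduced as repeated-measures analyses, the two Likert scales are described as measured at 3 and 12 months. Then: "These variables will be analysed by contingency table to compare the frequency of treatment success categories between the two randomised groups". The effect measure follows: "Results will be displayed as odds ratio with 95% CIs".

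The hypotheses for these scales have a direction. Surgery is expected to give superior treatment success, and for appearance the wording is "Less patient-rated bother with appearance at 12 months, 2, 5 and 10 years (measured on a 5-point Likert scale"). Both hypotheses begin at 12 months. So do both entries in the list of secondary outcomes.

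The table shells vary. Tables 4 and 5 (3 months) have one column for either a mean difference or an odds ratio; they carry treatment success but not bother with appearance. Tables 6, 7 and 11 to 13 (12 months) carry both scales, with a mean difference as the only effect column.

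**The concern.** There are three separate problems.

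1. **The test does not match the hypothesis.** A claim of more success or less bother concerns a shift along an ordered scale. A chi-squared test on five unordered categories asks only whether the two distributions differ in any way. It can be significant when neither arm is better overall, and it spreads its power over patterns that the hypothesis does not concern.
2. **The effect measure is undefined.** Two statisticians who follow this text faithfully could report different odds ratios from the same data. The choice would then fall at the analysis stage.
3. **The time points conflict.** A reader cannot tell whether 3-month data on these scales exist, for which scale, or whether they enter a comparison. A between-arm contingency table also makes no use of repeated measurements, so its place in that list has no analytic meaning.

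**Working it through.** **Inputs from the plan.** "A total of 128 patients (64 in each group) will provide 90% power to detect a difference of 14 points on the PRWE scale", and "We aim to recruit 160 patients to allow for 20% loss to follow-up". The inflation reproduces: 128 / (1 − 0.20) = 160. The trial reached "164 participants in the randomised trial and 136 in the observational study", so there are 164 / 2 = 82 per arm if nobody is lost. The calculations use 64 and 82 per arm. The plan states no power, category distribution or effect size for the Likert scales, so those inputs are assumed.

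**Is the odds ratio defined?** Take an assumed pair of distributions, best category first: 30/40/15/10/5% and 50/20/15/10/5%.
- Cut after the first category: (0.50/0.50) / (0.30/0.70) = 2.33.
- Cut after the second category: (0.70/0.30) / (0.70/0.30) = 1.00.

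One table gives two quite different odds ratios, and the plan does not say which is wanted.

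**What does ignoring the order cost?** Two-by-five tables were simulated, 10,000 per scenario. Pearson chi-squared (up to 4 df) was compared with the tie-corrected Wilcoxon rank-sum test, which stands in for an ordinal analysis. The second arm was obtained by multiplying every cumulative odds of the first by a common odds ratio. With an assumed 35/35/15/10/5% and 64 per arm:

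| Common OR | Chi-squared | Ordered test | Loss (points) |
|---|---|---|---|
| 1.5 | 13% | 24% | 11 |
| 2.0 | 34% | 57% | 23 |
| 2.5 | 57% | 79% | 22 |
| 3.0 | 74% | 91% | 17 |

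With no effect, the same set-up gave type I error of 4.7% and 4.9%.

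Across five assumed distributions (two skewed, one flat, one centred, one with 60% in the best category), the loss in points was:

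| Common OR | 64 per arm | 82 per arm |
|---|---|---|
| 1.5 | 10–11 | 12–13 |
| 2.0 | 19–23 | 22–24 |
| 2.5 | 20–24 | 16–24 |
| 3.0 | 14–22 | 9–18 |

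At an odds ratio of 1.25, with an assumed 25/35/20/12/8% and 64 per arm, power was 7% against 11%, a loss of 4 points.

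**Cross-check.** Give a 1-df and a 4-df test the same noncentrality, (1.960 + z_power)². For 80% power on 1 df this is (1.960 + 0.842)² = 7.85, and the 4-df test then has 59.5% power. For 1-df power of 50, 60, 70, 80 and 90%, the 4-df power is 31, 39, 48, 60 and 74%, a loss of 16 to 22 points.

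**Effects that do not follow the order.** For the 30/40/15/10/5% against 50/20/15/10/5% pair above, chi-squared has 59% power and the ordered test 31%. For a polarised change from 25/35/20/12/8% to 40/20/12/12/16%, chi-squared has about 60% and the ordered test under 10%.

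**Time points side by side.**

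| Place in the SAP article | Treatment success at 3 months | Bother at 3 months |
|---|---|---|
| Outcome variables | no | no |
| Study hypotheses | no | no |
| Secondary analysis, repeated-measures list | yes | yes |
| Tables 4 and 5 | yes | no |

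The tables agree with neither the outcome list nor the analysis text.

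**The case against.** The best defence is that these are two secondary outcomes on scales the plan itself calls non-standard, reported in an article based on a fuller plan that is not shown. The sentence on the Likert scales says contingency table, not unordered chi-squared; the test comes from the general rule. That is fair, but no other test for categorical data is named. The effect measure and table columns are also stated in the article itself, so the conflict is not detail left out by condensing.

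Three stronger readings are tempting and are not supported.

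- **A reader might infer that the plan loses a fixed 20 points of power.** It gives no distribution or effect for these scales. The loss is 4 points in one reasonable scenario and 24 in another, and the sign reverses for polarised effects.
- **A reader might infer that the odds ratio can only come from a cut-point chosen after seeing the data.** A proportional-odds model or category-specific odds ratios would also produce one. The analysts are to work with dummy group names until interpretation is complete, which limits choices that favour a treatment. It does not remove the choice, because the contrast between the two masked groups would still be visible.
- **A reader might infer that the plan intends mean differences of Likert categories.** The tables are offered as examples and the text says categorical outcomes get odds ratios. The shared column heading looks like a slip in the shells, but it needs correcting.

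**Conclusion.** The point holds in a limited form. Two parts rest on the text alone: the odds ratio for the Likert scales is undefined, and the 3-month time point is contradictory. The third part, the mismatch between an order-blind test and directional hypotheses, also follows from the text, but its size is conditional. If the arms differ by a proportional-odds shift, the loss is about 4 points at an odds ratio of 1.25, 10 to 13 at 1.5, 19 to 24 at 2 and 9 to 22 at 3; the figures from 1.5 upward cover 64 to 82 per arm. If the effect does not follow the order, chi-squared can be the stronger test. The primary PRWE analysis is untouched.

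**What to change.** Before unmasking, amend the plan as follows.

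- Name one ordinal analysis for each scale at 12 months: a proportional-odds model giving a common odds ratio with 95% CI, with the category frequencies alongside.
- Keep it unadjusted, or adjust for age group and gender. Do not enter the 19 sites as fixed effects: 128 / 19 is about 7 evaluable participants per site. A simulation of a site-adjusted model with assumed uneven site sizes and no true site effect gave a type I error of 7.7% and a median estimate of 2.19 for a true odds ratio of 2.0.
- Do not switch method on the result of a proportionality test; that would make the analysis depend on the data.
- Replace the mean-difference heading for these rows in Tables 6, 7 and 11 to 13 with this odds ratio.
- Take both scales out of the repeated-measures list.
- Reconcile the 3-month time point across the outcome list, the hypotheses, Tables 4 and 5 and the Secondary analysis text, according to what was actually collected.

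The cost is wording and table shells. The statistical price is a proportional-odds assumption and less sensitivity to differences that do not follow the order; the reported frequencies leave such differences visible.

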### Sensitivity analyses

In order to investigate the impact of missing data, a completed case analysis of the primary and secondary outcomes at 12 months will be performed and compared with the analysis using imputed data (if required); see Table 11 for example.

**Table 11 Tab11:** Sensitivity analysis. Primary and secondary outcomes at 12 months, based on completed cases analysis of randomised group

Outcome		Completed cases in randomised group		
		Surgical (*n*=__)	Non-surgical (*n*=__)	Mean difference (95%CI)
PRWE				
DASH				
ED-5D-5D, mean (SD)	EQ-UI			
	EQ-VAS			
Pain on NRS (0-10)				
Patient-reported treatment success n(%)	Very successful			
	Successful			
	Neutral			
	Unsuccessful			
	Very unsuccessful			
Patient-reported bother with appearance n(%)	Not at all			
	Bothered a little			
	Bothered moderately			
	Very bothered			
	Extremely bothered			
Radiographic measures, mean (SD)	Dorsal angulation (degrees)			
	Radial tilt (degrees)			
	Ulnar variance (mms)			
	Articular step (mms)			

In order to investigate the impact of non-compliance with the protocol, an as-treated analysis and a per-protocol analysis of the primary and secondary outcomes at 12 months will be performed and the results will be compared with the ITT analysis; see Tables 12 and 13 as examples. Non-operative treatment will be defined as a minimum of 28 days in the plaster splint for the purposes of the per-protocol analysis.

**Table 12 Tab12:** Sensitivity analysis. Primary and secondary outcomes at 12 months, based on as-treated analysis of randomised group

Outcome		As-treated allocation of randomised group		
		Surgical (*n*=__)	Non-surgical (*n*=__)	Mean difference (95%CI)
PRWE				
DASH				
ED-5D-5D, mean (SD)	EQ-UI			
	EQ-VAS			
Pain on NRS (0-10)				
Patient-reported treatment success n(%)	Very successful			
	Successful			
	Neutral			
	Unsuccessful			
	Very unsuccessful			
Patient-reported bother with appearance n(%)	Not at all			
	Bothered a little			
	Bothered moderately			
	Very bothered			
	Extremely bothered			
Radiographic measures, mean (SD)	Dorsal angulation (degrees)			
	Radial tilt (degrees)			
	Ulnar variance (mms)			
	Articular step (mms)

**Table 13 Tab13:** Sensitivity analysis. Primary and secondary outcomes at 12 months, based on per-protocol analysis of randomised group

Outcome		Per-protocol allocation of randomised group		
		Surgical (*n*=__)	Non-surgical (*n*=__)	Mean difference (95%CI)
PRWE				
DASH				
ED-5D-5D, mean (SD)	EQ-UI			
	EQ-VAS			
Pain on NRS (0-10)				
Patient-reported treatment success n(%)	Very successful			
	Successful			
	Neutral			
	Unsuccessful			
	Very unsuccessful			
Patient-reported bother with appearance n(%)	Not at all			
	Bothered a little			
	Bothered moderately			
	Very bothered			
	Extremely bothered			
Radiographic measures, mean (SD)	Dorsal angulation (degrees)			
	Radial tilt (degrees)			
	Ulnar variance (mms)			
	Articular step (mms)			

## Discussion

This plan describes the statistical analysis for CROSSFIRE. The primary analysis will determine whether surgery is superior to non-surgical treatment with respect to patient-reported wrist pain and function at 12 months. The secondary analyses will determine between-treatment differences at 3- and 12-month timepoints of outcomes including treatment complications and adverse events, patient-reported pain and function, quality of life, therapy utilisation, patient-reported treatment success, patient-reported bother with appearance and radiological outcomes. A sensitivity analysis will be conducted for potential biases, including a comparison between the observation and randomised arms of the study.

## Trial status

Participant recruitment was completed in January 2019 and collection of outcomes to 12 months post treatment is expected to be completed in December 2019. Data collection for 2-, 5- and 10-year outcomes will continue and will be analysed separately at a later date.

## Data Availability

A de-identified participant-level dataset and statistical code will be made available for collaborative research projects, on request of the chief investigator.

## Abbreviations

AO/OTA: Arbeitsgemeinschaft für Osteosynthesefragen/Orthopaedic Trauma Association
ANOVA: Analysis of variance
CI: Confidence interval
CRPS: Chronic regional pain syndrome
CROSSFIRE: A Combined Randomised and Observational Study of Surgery for Fractures In the distal Radius in the Elderly
DASH: Disabilities of the Arm, Shoulder and Hand
EQ-5D-5L: EQ-5D-5L; EuroQol instrument for assessing health status
ITT: Intention to treat
MCID: Minimal clinically important difference
MD: Mean difference
NHMRC: National Health and Medical Research Centre
NRS: Numerical Rating Scale
PRWE: Patient-rated wrist evaluation
RCT: Randomised controlled trial
SD: Standard deviation
VAS: Visual Analogue Scale
